## Abstract

**Background:**

The elderly population is expanding globally. This gives numerous challenges especially regarding hip fracture patients. In the US alone over 300.000 hip fracture patients are treated each year, and a large amount of those develop opoid addiction. Hip fractures require surgical intervention within 24 h and is associated with significant pain even at rest. Postoperative analgesic treatment need to be optimized to ensure adequate pain relief and to prevent subsequent opioid addiction. Previous studies have shown that methadone effectively decreases post-operative opioid consumption but the studies focused on younger patients undergoing elective surgery. This study focus on the use of methadone on the elderly, fragile patients undergoing acute surgery, by first determining the maximal tolerable dose.

The hypothesis is the maximal tolerable doses of these hip-fracture patients lies between 0.10 mg/kg and 0.20 mg/kg. This trial aims to estimate the maximum tolerable dose of methadone when administered to elderly patients undergoing surgery for a hip fracture.

**Method:**

This project is an adaptive dose-finding trial. The continuous reassessment method will estimate the maximum tolerable dose of methadone. The primary outcome will be respiratory depression. The statistical analysis plan will be published a priori to the closure of patient recruitment and statistical analysis of database results.

**Conclusion:**

The results of this study will give valuable information about the maximally tolerated dose of methadone for postoperative pain relief for elderly patients with hip fractures and potential adverse events.

This trial is registered on clinicaltrials.gov with trial registration: NCT05581901. Registered 17 October 2022, https://www.clinicaltrials.gov/ct2/show/NCT05581901?term=methadone&cond = hip&draw = 2&rank = 1.

## Introduction

1

### Background and rationale

1.1

Patients with hip fractures represent a vast population with substantial societal costs [1,2]. Danish hospitals encounter 140 hip fracture patients per 100,000 inhabitants per year, approximately 8000 fractures annually [3]. The median age of hip fracture patients is 81 years indicating that the fragile and elderly are greatly affected. In Denmark the 1-year mortality in hip fracture patients is rougly 30 %, with approximately 10 % of previously self-reliant patients referred to nursing homes after discharge [3]. Furthermore, half of all hip fracture patients experience a permanent decrease in gait function [4].

Hip fractures are classified as collum femoris fractures (50 %), pertrochanteric fractures (40 %) and subtrochantheric fractures (10 %). They all require surgical interventions within 24 h and are associated with significant pain even at rest [5]. Studies have indicated that postoperative pain is insufficiently treated in more than half of hip fracture patients, increasing the risk of chronic pain, delaying discharge and preventing early mobilization and rehabilitation [6].

Numerous studies suggest, that a single dose of methadone given during the surgery significantly ameliorates postoperative pain and reduces postoperative opioid consumption [[7], [8], [9], [10]]. However, these studies investigated younger patients undergoing elective surgery. At Hospital Sønderjylland (SHS), perioperative methadone is used for isolated cases, e.g., patients with chronic pain or high morphine tolerance. However, methadone is not part of routine care and is not used for the elderly. Therefore exploring the maximal tolerable dose (MTD) for elderly patients is clinically relevant.

The treatment of postoperative pain has been improved by a multimodal approach and using peripheral nerve blocks. However, supplemental opioids are often necessary, commonly taken months or years after surgery, and are an increasing healthcare challenge [11]. Consequently, patients undergoing surgery are at risk of experiencing side-effects and developing physical as well as psychological addiction to opioids [12]. The most common opioid-related side-effects include obstipation, nausea, itchy skin, dry mouth, vertigo, and sedation [7,12]. Therefore, opportunities to decrease the need for opioids in the postoperative phase are highly relevant.

In most studies, methadone is given perioperatively in dosages of 0.10–0.30 mg/kg and commenced at the induction of anaesthesia or surgery [7,10,13,14]. However, studies investigating the optimal dosage and time for administration reported that the patients receiving methadone after surgery needed twice as much opioid pain medication at postoperative day one compared to patients receiving methadone at induction of anaesthesia [13]. These studies also show that when using smaller dosages, such as 5–10 mg, the analgesic duration was only 3–4 h, compared with doses of 20 mg or more, which have a clinical effect closely related to the elimination half-life of 15–60 h without any increased risk for respiratory depression [13]. However, it is unclear how these doses are tolerated in an elderly and fragile population, and therefore the maximal tolerable dose needs to be determined.

## Aim

2

This trial aims to estimate the maximum tolerable dose of methadone when administered to patients *≥* 60 years undergoing surgery for a hip fracture.

## Statistical hypothesis

3

We hypothesize that the maximal tolerable dose of methadone for patients with a hip fracture lies between 0.10 mg/kg and 0.20 mg/kg.

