### Exposure

6.4

The exposure is a categorical variable where the groups are defined as:•0.10 mg/kg methadone at the beginning of surgery.•0.15 mg/kg methadone at the beginning of surgery.•0.20 mg/kg methadone at the beginning of surgery.

When patients are included from the ED the orthopaedic doctor will contact the primary investigator [name], who will assign each patient to a methadone group (0,10 mg/kg, 0,15 mg/kg or 0,20 mg/kg) using the model-based Continual Reassessment Method (CRM). This method uses registered primary outcome from the previous included patients or the prespecified prior if no data has been collected (see Fig. 1). The assigned methadone group is registered into REDcap and will be used to estimate the individual dose of methadone, which is calculated by multiplying methadone group with patient weight. This individual methadone dose will be written on a case report file (CRF). The primary care provider from the ED is responsible for withdrawing study medicine and placing the syringe near the patient together with the CRF. The individual dose of methadone is administered intravenously by the certified registered nurse anaesthetist when anaesthesia is commenced. The CRF will follow the patient to the orthopaedic ward.

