### Primary analysis and treatment assignment

7.2

This trial uses the Bayesian continual reassessment method, therefore stopping guidelines and probabilistic priors in relation to toxicity MTD (maximal tolerable dose) need to be determined before inclusion of the first patient. The stopping rules for the trial include:•If 40 persons are included.•If the probability of the lowest dose exceeding a predetermined toxicity threshold (set at 0.10) is greater than 95 % and more than 10 persons are included.•If the 95 % credibility interval of the toxicity level for the MTD is between 0 and 0.10 (a clinically acceptable toxicity level) and more than 10 persons are included.•If all the above stopping rules are fulfilled and 10 participants are included.

The predetermined toxicity threshold for the lowest dose considers the assumption that toxicity increases with higher doses. Thus, if the toxicity at the lowest dose surpasses the clinically acceptable level of 0.10, further dose escalation should be avoided. The pre-specified prior to this analysis consists only of presumed toxicity levels of the different doses and the alpha parameter. The presumed toxicity levels for the three doses is set to 0.05, 0.1, and 0.2 for 0.10 mg/kg, 0.15 mg/kg, and 0.2 mg/kg, respectively, and alpha follows a *γ*(1*,* 1) distribution. After the specification of the prior and stopping rules, the method uses the dose-response curve to escalate or deescalate the doses in a non-conservative manner (see Fig. 2) and close arms if one or more stopping rules are met. The 1-parameter model estimates the MTD more efficiently by escalating through the doses faster [16]. This is acceptable because the risk of adverse events by respiratory depression is low. Furthermore, there may be difficulties fitting the model or obtaining consistent estimates of model parameters in a two-parameter model [16]. Thus, we choose to use the 1-parameter model for this study.

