## Discussion

8

The results of this study will provide important evidence on the analgesic safety measures of methadone during hip surgery. The maximal tolerable dose will be used in a future randomized clinical trial. This knowledge is essential when aiming to improve the treatment of hip-fracture patients. The study will run in a real-life setting to increase the feasibility of implementing the methods afterwards. This pre-defined SAP is essential to increase the study's transparency and explicitly describe protocol deviations to increase reproducibility and avoid any risk of reporting bias or data-driven analysis.

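### The hypothesised range is the tested dose range, so a low-toxicity trial would be reported as an MTD of 0.20 mg/kg when the data show that the MTD was not reached

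*SAP article*

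**What the plan says.** Section 3 of the SAP article gives the hypothesis: "We hypothesize that the maximal tolerable dose of methadone for patients with a hip fracture lies between 0.10 mg/kg and 0.20 mg/kg". Section 6.4 lists three exposure groups, the highest being "0.20 mg/kg methadone at the beginning of surgery"; the other two are the lower end and the midpoint of the same interval.

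Section 7.2 fixes the prior: "The presumed toxicity levels for the three doses is set to 0.05, 0.1, and 0.2 for 0.10 mg/kg, 0.15 mg/kg, and 0.2 mg/kg, respectively". The single model parameter has a Gamma(1,1) prior. On the model the section says: "Thus, we choose to use the 1-parameter model for this study". It does not say whether this is a power or a logistic model, or whether doses are chosen by posterior mean or plug-in estimate.

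Three stopping rules in 7.2 matter here: a cap of 40 patients; a stop when the probability that the lowest dose exceeds 0.10 toxicity is above 95%; and a stop when the 95% credible interval for toxicity at the MTD lies between 0 and 0.10. The last two need more than 10 patients. Section 7.4 sets the target toxicity to 0.10. Section 7.5 promises 95% credible intervals for the MTD and for toxicity at the dose. Section 8 adds: "The maximal tolerable dose will be used in a future randomized clinical trial".

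**The concern.** A hypothesis about where the MTD lies is informative only if the analysis can place it elsewhere. Here the hypothesised interval and the dose grid coincide. The plan can find that even the lowest dose is too toxic, which would place the MTD below the range. It has no rule or wording for an MTD above the range.

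The third stopping rule sharpens this. An interval for toxicity at 0.20 mg/kg that lies wholly below the target means that the dose with 10% toxicity is above 0.20 mg/kg. Followed as written, the plan stops there and keeps 0.20 mg/kg as the MTD. Two different conclusions, that the MTD is about 0.20 mg/kg and that it was not reached, would be reported in the same words, and the result goes into a later randomised trial.

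**Working it through.** **The plan's own figure.** The plan prints no operating characteristic on this point. Its one design figure is the 40 patients in 7.4 (target 0.10, accuracy 0.6, odds ratio 2). The cited formula is not printed, so it cannot be rerun. Simulated accuracy at 40 patients is 0.63 to 0.69, consistent with 0.6. The sample size is not at issue.

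**The structural step.** Doses that can be named: 0.10, 0.15 and 0.20 mg/kg. Hypothesised interval: 0.10 to 0.20 mg/kg. The probability of naming an MTD above 0.20 mg/kg is 0 for any model, estimator or sample size.

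**What the third rule means at the top dose.** If the upper limit of an equal-tailed 95% interval for toxicity at 0.20 mg/kg is below 0.10, the posterior probability that this toxicity is below target exceeds 0.975.

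**The hypothesis in the model.** Assume the power form, toxicity = (presumed toxicity)^alpha. The MTD lies within the range when 0.05^alpha ≤ 0.10 ≤ 0.20^alpha:

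- lower bound: ln 0.10 / ln 0.05 = 0.769
- upper bound: ln 0.10 / ln 0.20 = 1.431

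With alpha ~ Gamma(1,1), the prior probabilities are 1 − exp(−0.769) = 0.536 below the range, exp(−0.769) − exp(−1.431) = 0.225 within it, and exp(−1.431) = 0.239 above it. The same three probabilities can be read from the posterior. They are informative where the named dose is not. The median posterior probability of *within* is about 0.76 to 0.78 when the true rates equal the plan's presumed 5/10/20%, and about 0.02 to 0.06 when they are 0.5/1/2% or 1/2/3%.

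**Simulation.** Presumed toxicities and prior as stated; cohorts of one; next dose closest to 0.10; the three stopping rules above. Four variants: power or one-parameter logistic (intercept 3, an assumption), each with posterior-mean or plug-in estimate. True rates are assumptions, because the article gives no event rate.

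| True toxicity at 0.10 / 0.15 / 0.20 mg/kg | 0.20 mg/kg named | 0.20 mg/kg named and 95% interval wholly below 0.10 |
|---|---|---|
| 0 / 0 / 0 | 100% | 100% (stops at 17 to 31 patients, by variant) |
| 0.5 / 1 / 2% | about 99 to 100% | about 58 to 73% |
| 1 / 2 / 3% | about 94 to 99% | about 44 to 61% |
| 2.5 / 5 / 10% (MTD truly 0.20 mg/kg) | about 62 to 76% | about 6 to 7% (power); about 15 to 21% (logistic) |

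If a zero-toxicity trial ran on to 40 patients, the upper limit at 0.20 mg/kg would be 0.04 to 0.075, still below target, with 0.20 mg/kg named.

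**The lower end, for comparison.** With true toxicity 30/40/50% the lowest-dose rule stops 96 to 97% of trials, and with 20/30/40% about 67 to 71%. The hypothesis can be contradicted from below.

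**The case against.** Three points against the concern have weight.

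*A reader might infer that a low-toxicity trial will confirm the hypothesis.* The document does not say so. Sections 7.2 and 7.5 contain no rule that the named dose supports the hypothesis, and no test of it. The aim in section 2 is estimation. The inference also needs the word between to include the endpoint 0.20. What stands is that a section headed as a statistical hypothesis has no stated link to the analysis, so that inference is left open.

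*Any CRM names a dose from a finite set, and the intervals in 7.5 would show toxicity at 0.20 mg/kg well below 10%.* Both are true, and the second softens the defect. But an interval fixes no conclusion, and the third stopping rule treats just this interval as grounds to stop with the dose as MTD.

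*The low-toxicity case is hypothetical.* A reader might take the phrase "without any increased risk for respiratory depression" in 1.1 as evidence that toxicity will be low. It compares larger with smaller doses in the cited studies, and the same section describes the earlier methadone studies as being in younger, elective patients. The next sentence calls tolerance in the elderly unclear, and the prior presumes 20% at the top dose. Better support is in 7.2, which calls the risk of respiratory depression low. The case is plausible, not established.

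A reader might also fear that an over-toxic dose is carried forward. This defect does not do that: in the case described, 0.20 mg/kg has toxicity below the plan's limit and is merely not shown to be maximal.

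**Conclusion.** The point holds as a reporting gap that should be fixed. The plan cannot name an MTD above the hypothesised range. Its third stopping rule retains 0.20 mg/kg as the MTD on data showing that the MTD was not reached. The structural part depends on no model choice. The size, about 94 to 100% of trials naming 0.20 mg/kg, rests on assumed true toxicity of 0 to 3% at that dose and varies with the model and estimator. Dose assignment, stopping, sample size and the posterior itself are unaffected.

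**What to change.** Amend the SAP before the analysis, without changing doses, assignment, stopping or sample size.

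1. In 7.2 and 7.5, report three posterior probabilities: toxicity at 0.10 mg/kg above 0.10 (MTD below the range); toxicity at 0.10 mg/kg at most 0.10 and at 0.20 mg/kg at least 0.10 (within); toxicity at 0.20 mg/kg below 0.10 (above).
2. State that the named dose alone is not support for the section 3 hypothesis.
3. Prespecify that, when 0.20 mg/kg is selected and its 95% credible interval for toxicity lies wholly below 0.10, the result is reported as *MTD not reached within the tested range*. Use this limit, already in the third stopping rule, and not a looser cut-off. A posterior probability above 0.90 would give the label in about 11 to 14% of trials whose true MTD is 0.20 mg/kg under the power model.
4. State the model form and the estimator, because the figures depend on them.

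The cost is wording and a few lines of output from the existing posterior. The conclusion becomes less definite. The *within* probability is often indecisive when the true MTD is at an end of the range (median about 0.55 under the power model, 0.45 to 0.52 under the logistic). With the true MTD at 0.20 mg/kg, about 6 to 7% of trials would be labelled not reached under the power model, and more under the logistic model tried (about 15 to 21%). With true toxicity of 1/2/3%, about 39 to 56% of trials would not earn the label, which is why the three probabilities should be reported in every case.

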## Objective

4

The trial estimates the maximal tolerable dose by investigating the risk of respiratory depression in the first 24 h after surgery for patients *≥* 60 years undergoing surgery for a hip fracture. The secondary objectives include how the methadone doses are tolerated in regard to side effects and consumption of rescue medication.

## Study methods

5

### Study design, setting and recruitment

5.1

A single-centre adaptive dose-finding trial will be conducted. The recruitment will, according to the plan, commence in November 2022. All hip fracture patients from the regional Hospital Sønderjylland orthopaedic or emergency department will be invited to participate. The on-duty orthopaedic personnel will recruit patients and ensure the patient receives written and verbal information about the study. The patients will be offered 2 h to consider participation.

### Inclusion and exclusions criterias

5.2

#### Inclusion criteria

5.2.1

•Patients presenting with a hip fracture in the emergency department (collum femoris fractures, pertrochanteric fractures and subtrochanteric fractures. ICD-10-codes: DS720-722)•Age *≥* 60 years•Patients must be able to reliably assess their pain level using the Verbal Rating Scale (VRS) and be able to ask for supplementary analgesics as needed•Patients must be able to read and speak Danish and understand the information and be able to give informed consent

#### Exclusion criteria

5.2.2

•Polytrauma (defined as severe injuries to multiple body regions) or multiple indications for surgical intervention (defined as one or more absolute indications for surgical intervention besides the hip fracture).•Previous allergic reactions or hypersensitivity towards methadone hydrochloride or sodium-chloride.•Contraindications for methadone treatment, i.e. chronic obstructive pulmonary disease (Gold classification C + D [15]), history with acute asthma attacks or atopic skin conditions, cor pulmonale, raised intracranial pressure or head injury, pheochromocytoma, history with paralytic ileus, QT interval prolongation, myasthenia gravis, liver disorders or hypotension.•Concurrent administration with monoamin oxidase (MAO) inhibitors or within 2 weeks of suspending treatment with these medicinal products.•Concurrent administration of sedatives, e.g. benzodiazepines or related drugs.•Included in other studies.•Current drug addiction, e.g., opioid addiction or intravenous addiction.

### Study population characteristics

5.3

The variables will be presented in a baseline table (see Table 1). Descriptive statistics are presented below in section 7.1 and used to assess reproducibility of our data to other settings.

**Table 1 tbl1:** Baseline table.

Variables	Methadone dose group			P-value
	0.10 mg/kg	0.15 mg/kg	0.20 mg/kg	
*Hip fracture type*				
Collum femoris fracture DS720	xx (xx,x%)	xx (xx,x%)	xx (xx,x%)	*△ or***┼**
Pertrochanteric fracture DS721	xx (xx,x%)	xx (xx,x%)	xx (xx,x%)	*△ or***┼**
Subtrochanteric fracture DS722	xx (xx,x%)	xx (xx,x%)	xx (xx,x%)	*△ or***┼**

*Demographic data*				
Age	xx ± xx	xx ± xx	xx ± xx	* *or ₼*
Sex	xx (xx,x%)	xx (xx,x%)	xx (xx,x%)	*△ or***┼**
ASA (American Society of Anesthesiologists) classification	xx (xx,x%)	xx (xx,x%)	xx (xx,x%)	*△ or***┼**

*Lifestyle*				
Weight (BMI)	xx ± xx	xx ± xx	xx ± xx	* *or ₼*
Tobacco	xx (xx,x%)	xx (xx,x%)	xx (xx,x%)	*△ or***┼**
Alcohol	xx (xx,x%)	xx (xx,x%)	xx (xx,x%)	*△ or***┼**
Chronic use of opioids	xx (xx,x%)	xx (xx,x%)	xx (xx,x%)	*△ or***┼**

*Comorbidities*				
Congestive and chronic heart failure	xx (xx,x%)	xx (xx,x%)	xx (xx,x%)	*△ or***┼**
Cardiac arrhythmias	xx (xx,x%)	xx (xx,x%)	xx (xx,x%)	*△ or***┼**
Valvular disease	xx (xx,x%)	xx (xx,x%)	xx (xx,x%)	*△ or***┼**
Pulmonary circulation disorders	xx (xx,x%)	xx (xx,x%)	xx (xx,x%)	*△ or***┼**
Peripheral vascular disorders	xx (xx,x%)	xx (xx,x%)	xx (xx,x%)	*△ or***┼**
Hypertension, uncomplicated	xx (xx,x%)	xx (xx,x%)	xx (xx,x%)	*△ or***┼**
Hypertension, complicated	xx (xx,x%)	xx (xx,x%)	xx (xx,x%)	*△ or***┼**
Paralysis	xx (xx,x%)	xx (xx,x%)	xx (xx,x%)	*△ or***┼**
Other neurological disorders	xx (xx,x%)	xx (xx,x%)	xx (xx,x%)	*△ or***┼**
Chronic pulmonary disease	xx (xx,x%)	xx (xx,x%)	xx (xx,x%)	*△ or***┼**
Diabetes, uncomplicated	xx (xx,x%)	xx (xx,x%)	xx (xx,x%)	*△ or***┼**
Diabetes, complicated	xx (xx,x%)	xx (xx,x%)	xx (xx,x%)	*△ or***┼**
Hypothyroidism	xx (xx,x%)	xx (xx,x%)	xx (xx,x%)	*△ or***┼**
Renal failure	xx (xx,x%)	xx (xx,x%)	xx (xx,x%)	*△ or***┼**
Liver disease	xx (xx,x%)	xx (xx,x%)	xx (xx,x%)	*△ or***┼**

Statistical test for the p-value.

*∗ Anova*.

**┼***χ*^*2*^.

*△ Fischer's exact*.

*₼ Kruskal-Wallis test*.

## Variables

6

### Baseline variables

6.1

For safety and reproducibility purposes, the baseline variables presented in Table 1 will be noted for each given methadone dose in the trial (see Table 2).

**Table 2 tbl2:** Secondary analysis.

Secondary analysis					
Variable	Level			Coef (95%CI)	p-value
Length of stay Pain	0.10 mg/kg 0.15 mg/kg 0.20 mg/kg 0.10 mg/kg 0.15 mg/kg 0.20 mg/kg			Ref. Ref.	n.a n.a
Variable	Level			IRR (95%CI)	p-value
Consumption	0.10 mg/kg	at	6 h	Ref.	
	0.15 mg/kg	at	6 h		
	0.20 mg/kg	at	6 h		
	0.10 mg/kg	at	24 h	Ref.	
	0.15 mg/kg	at	24 h		
	0.20 mg/kg	at	24 h		
	0.10 mg/kg	at	72 h	Ref.	
	0.15 mg/kg	at	72 h		
	0.20 mg/kg	at	72 h		
Respiratory depression	0.10 mg/kg			Ref.	n.a
	0.15 mg/kg				
	0.20 mg/kg				
Variable	Level			OR (95%CI)	p-value
Side effects	0.10 mg/kg	at	6 h	Ref.	
	0.15 mg/kg	at	6 h		
	0.20 mg/kg	at	6 h		
	0.10 mg/kg	at	24 h	Ref.	
	0.15 mg/kg	at	24 h		
	0.20 mg/kg	at	24 h		
	0.10 mg/kg	at	72 h	Ref.	
	0.15 mg/kg	at	72 h		
	0.20 mg/kg	at	72 h		

### Primary outcome

6.2

The primary outcome is the incidence of respiratory depression during the first 24 h after surgery. Respiratory depression is defined as a respiratory frequency below 10 breaths pr. minute and peripheral oxygen saturation below 94 % despite 4 ltr/min oxygen and will be registered upon arrival at the orthopaedic ward and again 6 and 24 h after surgery.

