### Secondary outcomes

6.3

The secondary outcomes include:•Length of stay, defined as the number of hours spent at the PACU.•Number of times administration of antidote Naloxone was necessary.•Consumption of opioid rescue medication measured upon arrival at the orthopaedic ward and after 6, 24, and 72 h postoperatively.•Opioid-related side effects, including post-operative nausea and vomiting (PONV), measured upon arrival at the orthopaedic ward and after 6 and 24 h postoperatively.•Postoperative pain will be measured using VRS upon arrival at the orthopaedic ward and after 6, 24, and 72 h postoperatively.

The primary and secondary outcomes will be measured by trained healthcare personnel at the orthopaedic department and recorded in RedCap (Research electronic data Capture). In addition, [name] will note the starting dose and whether the patient experienced toxicity in the dose-escalation program.

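### The 24 h toxicity outcome that drives the CRM is registered at only three times, with no stated look-back, PACU source or use of naloxone records, so any missed event biases the MTD upward

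*SAP article*

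**What the plan says.** Section 6.2 states the estimand: "The primary outcome is the incidence of respiratory depression during the first 24 h after surgery". The criteria are momentary vital signs: a respiratory frequency below 10 per minute together with a saturation below 94 % despite oxygen. The outcome "will be registered upon arrival at the orthopaedic ward and again 6 and 24 h after surgery".

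Section 6.3 adds: "The primary and secondary outcomes will be measured by trained healthcare personnel at the orthopaedic department". It lists as secondary outcomes "Length of stay, defined as the number of hours spent at the PACU" and "Number of times administration of antidote Naloxone was necessary". Neither is part of the toxicity definition in 6.2.

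Section 6.4 has methadone "administered intravenously by the certified registered nurse anaesthetist when anaesthesia is commenced". On what feeds the dose assignment it says: "This method uses registered primary outcome from the previous included patients or the prespecified prior if no data has been collected". Section 7.2 builds the stopping rules on the same toxicity model, and section 8 carries the resulting dose into a future randomised trial.

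**The concern.** The estimand covers a whole window, but the stated data collection is three points. Methadone is given at the start of anaesthesia and the first listed registration is at ward arrival, so the time in the PACU lies after dosing and before the first registration. The second and third registrations are 18 h apart (24 − 6). A patient who met the criteria in the PACU or at 3 h, was treated and then breathed normally at the listed times would not meet the criteria at any of them.

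This binary record is the only patient outcome the CRM uses. It decides each next dose, both probability-based stopping rules and the MTD. The error has one direction: a missed event turns a toxic record into a non-toxic one, and nothing in the schedule produces the reverse. With at most 40 patients and escalation that section 7.2 describes as non-conservative, single records carry weight.

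**Working it through.** **Inputs from the SAP article.** Presumed toxicities 0.05, 0.10 and 0.20 for 0.10, 0.15 and 0.20 mg/kg; one-parameter model; alpha ~ Gamma(1,1); maximum 40 patients; stop if P(toxicity at lowest dose > 0.10) > 95 %, or if the 95 % credibility interval at the MTD lies within 0 to 0.10, each with more than 10 patients (all 7.2); target 0.10, accuracy 0.6, odds ratio 2 (7.4).

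**Assumptions.** Capture fraction s, the share of truly toxic patients who are recorded as toxic (not in the document; range shown). Model form p_d = skeleton_d^alpha. Plug-in of the posterior mean of alpha, with the posterior mean of p as a variant. Start at 0.10 or 0.15 mg/kg.

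**The plan's own figure.** The sample-size formula is cited but not printed, so N = 40 cannot be reproduced exactly. Simulating this CRM without early stopping, over three scenarios with odds ratio 2 between adjacent doses, gives an average accuracy at n = 40 of 0.663 (plug-in) or 0.628 (posterior mean). N = 40 is consistent with the stated 0.6, and the point here does not depend on it.

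**Weight of one record.** Take three patients at 0.15 mg/kg (skeleton 0.10, ln 10 = 2.3026).

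- 0 of 3 recorded: the posterior is proportional to e^(−a)(1 − 0.1^a)^3. Its mean is [1 − 3/3.3026² + 3/5.6052² − 1/7.9078²] / [1 − 3/3.3026 + 3/5.6052 − 1/7.9078] = 0.8044/0.5004 = 1.61. Plug-in toxicities are 0.05^1.61 = 0.008, 0.1^1.61 = 0.025 and 0.2^1.61 = 0.075. The nearest to 0.10 is the top dose, so the next patient gets 0.20 mg/kg.
- 1 of 3 recorded: the mean is [1/3.3026² − 2/5.6052² + 1/7.9078²] / [1/3.3026 − 2/5.6052 + 1/7.9078] = 0.0440/0.0724 = 0.61. Plug-in toxicities are 0.16, 0.25 and 0.38, so the next patient gets 0.10 mg/kg.

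One missed event therefore moves the next assignment from the lowest dose to the highest.

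**Whole trial.** If the true toxicity at dose d is p_d, the recorded toxicity is s × p_d. Simulated trials used the maximum of 40 and the two probability rules. Ranges cover runs that differ in start dose, random seed and details of coding.

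| Capture s | 0.20 mg/kg named MTD, true toxicity 0.05/0.10/0.20 |
|---|---|
| 100 % | 18–21 % |
| 90 % | 26–27 % |
| 80 % | 37 % |
| 70 % | 47–51 % |
| 50 % | 72–74 % |

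The posterior-mean variant gives 15 % at full capture and 63 % at half capture, so the direction does not depend on the estimator.

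**Safety stop.** With true toxicity 0.20/0.30/0.45, so that every dose exceeds the target, the stop fires in 71–74 % of trials at full capture and 11–12 % at half capture.

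**The case against.** The strongest reply is that the text can be read as interval recording. To register an outcome at 6 h may mean entering what happened since the last entry. Several places favour this:

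- Section 6.3 uses the same times for rescue opioid consumption, which has to be accumulated over an interval.
- The ward staff who measure the primary outcome are also named for PACU hours and naloxone counts, so they must obtain PACU information in some way. The inference that ward staff cannot cover the PACU therefore fails.
- Section 6.4 has the case report file follow the patient from theatre to the ward.
- What goes into the dose-escalation program is a patient-level toxicity status (6.3), and Table 2 shows respiratory depression without time points.
- Monitoring and look-back instructions may stand in the protocol.

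This stands as far as it goes. A reader might infer that the plan does code PACU events and naloxone-treated events as non-toxic. No sentence says so. Nor are naloxone events hidden, since section 7.3 analyses them by dose. But the article itself fixes the endpoint, the times, the staff and the CRM input, and states neither a look-back nor a rule for combining sources. The interval reading has to be inferred.

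A second reply is that the simulation shows what lost events would do, not that any are lost. That is correct. At 90 % capture the effect is modest: the middle dose is still chosen in about 55 % of trials, against about 56 % at full capture.

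A third is that counting naloxone use makes a composite outcome. With a look-back, a patient who met the criteria before naloxone already counts, so naloxone serves mainly as a prompt to check the record.

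**Conclusion.** The point holds as an ambiguity with a one-sided consequence. Section 6.2 promises a 24 h incidence, and its stated registration does not secure one. If followed literally, recorded toxicity can only be too low, the MTD too high and the safety stop too weak.

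The direction is firm and the size is not. The chance of naming a dose with twice the target toxicity runs from about 20 % at full capture to 26 % at 90 %, 37 % at 80 %, about 50 % at 70 % and 74 % at 50 %. These figures assume that the plan's presumed toxicities are true and that the CRM works as set out above. The document does not say where in this range the trial lies, so a reader should not infer from the lower rows that the MTD will probably be wrong.

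Because an interval reading is possible, this is something that should be fixed, with moderate confidence, rather than a demonstrated failure of the design.

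**What to change.** In section 6.2, state that a patient counts as toxic for the CRM if the existing criteria are met at any time from the end of surgery to 24 h, PACU included. Name the records used, and say that ward arrival, 6 h and 24 h are the times at which the records since the previous time are read. Add that a naloxone administration in that window prompts a check of whether the criteria were met, and is coded as an event if it was given for respiratory depression. Keep the naloxone count as a secondary outcome. If the protocol already says this, one sentence bringing it into 6.2 is enough.

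The cost is wording, a case report form entry and the reading of routine PACU records; that these are available is an assumption. The observed toxicity rate would rise by a factor of 1/s: about 1.1 if 90 % of toxic patients would otherwise have been caught, and 2 if 50 %. No dose or clinical rule changes.
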